### Interventions

The two intervention arms (*n* = 150 participants in each arm) are going to contain the same strength and balance activities as well as principles and habitualization strategies as described in the original LiFE program manual [35], but will use different approaches of delivery (i.e., group vs. individual). The intervention sessions in both arms are going to be conducted by physio therapists, occupational therapists and/or sports scientists. Trainers attended a two-day workshop to ensure standardised delivery of all gLiFE and LiFE intervention components and were tested and awarded certification prior to the start of the intervention delivery. A detailed description of the intervention components is provided using the TIDieR checklist [36] (Table 2); a schematic overview of the seven sessions is presented in Table 3.

**Table 2 Tab2:** Template for Intervention Description and Replication (TIDieR) checklist

Item No.; Name	Description	
1. Brief name	Lifestyle-integrated Functional Exercise (LiFE): individually delivered (LiFE) and group-delivered (gLiFE)	
2. Why	The LiFE program was shown to be effective in reducing falls while at the same time improving balance, strength, and enhancing physical activity. Due to high economic requirements regarding the program’s delivery, a group-based delivery of the program is tested to evaluate whether a more cost-effective approach can be successful.	
3. What: Materials	Participant’s manual, German version [42]; used during and after intervention: Contains descriptions and instructions of all LiFE activities; principles of balance and strength training as well as physical activity enhancement; precautions and safety instructions when performing the activities; background on balance and strength exercise; assistance and support for changing habits and performing LiFE activities. Trainer’s manual, German version; one for LiFE, one for gLiFE. Contains all information also included in the participant’s manual; additionally: complete outline of all 7 sessions and 2 phone calls, including text templates, material, preparations, and precautions. Working book; for all participants; used during intervention: Includes information on study procedures, personnel, contacts, and safety instructions; activity planning sheets for balance, strength, and physical activity; notes pages; LiFE principles; ‘life compass’ LiFE Assessment Tool (modified Version in German); for trainers; used to determine individuals’ performance level of LiFE activities Laminated cards, showing LiFE principles and LiFE activities to be used as visual aids during intervention sessions. Further materials to be used in interventions sessions: balls, blankets, sponge rubber, boxes, clipboards, pens, bags, name tags, flipcharts.	
4. What: Procedures	LiFE 7 home visits by one qualified trainer, 2 telephone calls 4 and 10 weeks after last session.	gLiFE 7 group sessions (n = 8–12 participants) led by one main and one co-trainer, 2 telephone calls 4 and 10 weeks after last session.
	In both intervention arms, LiFE activities, identification of daily situations to integrate activities, their selection, implementation, and upgrading are addressed. In session 1, 4 LiFE activities are introduced; in each subsequent session, 2 other new activities are added. One theoretical lesson is given in each session; topics are: (1) LiFE principles, (2) cues and prompts, (3) upgrading, (4) coping planning, (5) resources for habit formation, (6) mindfulness vs. habit, and (7) long-term success with LiFE. Action planning and implementation intentions are addressed at the end of each session. To compensate for not being in the individual’s home and the lack of knowledge on the person’s environment, in gLiFE, visualization techniques are used to support and facilitate action planning as well as habit formation.	
5. Who provided	Trainers are either sport scientists, physiotherapists, occupational therapists or psychologists. All trainers received a two-day training course on the program background, aims, and components prior to the project start.	
6. How	After randomization, the intervention is provided either in a one-to-one situation in the participant’s home or in a group setting with 8–12 participants.	
7. Where	Two study sites: Heidelberg and Stuttgart (Germany).	
	LiFE Delivered in participants’ homes in suburban Heidelberg area (max. 15 km from the city centre) / one large city district in Stuttgart.	gLiFE Participants attend sessions at the Network Aging Research (Heidelberg) / rented rooms near the recruitment district in Stuttgart.
8. When and how much	LiFE 7 sessions within 11 weeks: week 1, 2, 3, 5, 7, 9, 11. Two telephone calls 4 and 10 weeks after the last session (i.e., week 15 and 21). Duration of each session: 1–1.5 h.	gLiFE see LiFE. Duration of each session: 2–2.5 h.
	Intensity and dose are determined by the individuals’ activity plans, adherence, and performance level of each activity.	
9. Tailoring	In (g)LiFE, irrespective of its method of delivery, individual tailoring is constantly given due to the activities’ integration into the subjects’ personal routine. LiFE activities, their frequency and intensity are determined by the participants and their situation in which the activities are integrated.	
10. Modifications	n.a.	
11. How well: Planned	To assess adherence to i/gLiFE, participants fill out the Exercise Adherence Rating Scale (EARS; [63]) on a monthly basis. Completed forms are then sent to the study centres in Heidelberg and Stuttgart by mail. Activity planning sheets used during the intervention phase also contain check boxes for each day (*activity completed as planned* vs. *not completed as planned*). Fidelity of the intervention delivery is pursed by providing a comprehensive trainer’s manual, in which each intervention session is outlined in large detail to ensure standardized delivery of all intervention components. All trainers have received a two-day training course.	
12. How well: Actual	n.a.

**Table 3 Tab3:** Structure of the 7 intervention sessions in LiFE and gLiFE

	1	2	3	4	5	6	7
Aim	Introduction	Determination of activities, habit formation and problem solving					
Intro	Familiarization	Repetition of the learned exercises, most positive experiences and greatest challenge in the execution of LiFE					
Main part	LiFE principles	Cues, prompts	Upgrading	Coping planning	Resources for habit formation	Physical activity	Long-term success with LiFE
	LiFE activities: −4 activities (tandem stand, tandem walk, sit to stand, squatting) -practice 2 of them [1 balance/1 strength]	Mediation of two new LiFE activities -practice the activities -keep/skip?					Repetition LiFE activities
		-leaning -walking on toes	-stepping over objects -walking on heels	-walk more -climbing stairs	-tighten muscles -one-leg stand	-move sideways -sit less	
	Action planning/implementation intentions						
End	Assessments, wrap-up & “homework”						

#### Individual LiFE (LiFE)

In LiFE, the program will be taught in seven individual home visits within 11 weeks, as described in the original LiFE program manual [35]. Each home visit is going to take between 1 and 1.5 h. Trainers are going to present a total of five balance activities, seven strength activities for the lower extremities, and two activities to increase general PA are presented. Participants are going to learn how to implement the LiFE activities into their daily routine and how to independently execute the activities, including selection, upgrading, and identification of daily situations to integrate activities. In addition to the home visits, all participants are going to receive two ‘booster telephone calls’ four and 10 weeks after the last intervention session.

#### Group LiFE (gLiFE)

gLiFE will consists of seven group sessions (*n* = 8–12 participants) which are held over the course of 11 weeks, with a duration of about 2 h per session. Each session is going to be led by one main and one co-trainer. In all group sessions, trainers are going to teach the participants how to perform and integrate LiFE activities into their personal daily routine in congruence with LiFE. After the group sessions have ended, participants will also receive two booster telephone calls as in LiFE (see Fig. 1).

**Fig. 1 Fig1:**
[figure not shown]
SPIRIT participant flow chart; ^†^in Stuttgart, a health insurance company additionally contacted their members who matched the inclusion criteria

Based on predefined criteria by Moore et al. [31], the conceptualisation of the gLiFE program was performed by an interdisciplinary team consisting of sports scientists, psychologists, geriatricians, occupational therapists, and physio therapists in close consultation with one of the originators of the LiFE program ([name]) and the lead investigator of a previous approach to adapt LiFE to a group setting [37]. In addition, the Health Action Process Approach (HAPA) [38]—as an established model to explain health behaviour—was used and extended to support the adaptation of the original LiFE components to the requirements of the group format, with emphasis on intention quality and habit formation [39, 40]. Trainers received a two-day workshop to ensure standardised intervention delivery in both study sites. The final gLiFE concept was piloted in a sample of community-dwelling older adults who matched the criteria of the envisaged sample in the trial. The pilot used a mixed-method approach including quantitative and qualitative (focus group) questions for estimating feasibility and refinement of the intervention before drawing up the final versions of the trainer’s manuals for LiFE and gLiFE. These were drafted following the already existing manual by Clemson et al. [35] to ensure reproducibility of all intervention components and facilitate intervention conduct and organisation. Trainer’s manuals include a complete outline of each session, instruction, and exemplary transcriptions to achieve high fidelity and facilitate uniform implementation. The LiFE participant’s manual [41] has been translated into German language by experts involved in LiFE-related projects [42].

#### Participant safety and adverse events

All study participants will receive specific guidelines for safe training (shoes, support options, lighting, etc., described in the LiFE manuals). Serious adverse events / reactions and adverse events / reactions will be monitored throughout the study to assess the safety of the trial and manage participant risk. Adverse events related or potentially related to study participation will be reported to the responsible Ethic Review Board.

### Outcomes

A complete list of screening and outcome parameters and descriptive variables is provided in Table 4. Data include socio-demographics, medical and medication information, neuropsychological status, motor function, health status and economics, physical activity status, psychosocial data, and information on adherence to LiFE activities and group evaluation. To ensure highest possible standardisation of assessments, instructors attended a two-day workshop covering all aspects of screening and assessments.

**Table 4 Tab4:** Overview of descriptive variables and assessment measures over the course of the study

		TS	IS	BA	Int	FU6	FU12
	Socio-demography						
	Age; birthday; gender; living conditions (institutionalised vs. community-dwelling)	x					
	Living alone or not; marital status; school-leaving qualification; years of education; academic grades; retirement age		x				
	German-speaking	x					
	Medical and medication information						
	Height; weight		x			x	x
	Blood pressure^f^		x				
	Vision impairment: *Are you able to read a newspaper or book, with or without visual aid?*	x					
	Hearing impairment (whisper test)		x				
	Fall history and fall-related injuries in the past 12 months	x					
P	Fall calendar^d^ [43]						
	Prevalence of neurologic, pulmonary or cardiac disease	x					
	Comorbidities incl. Treatment; cardiac issues or stroke in past 6 months; pain while walking and resting; blood pressure [mmHg]; pulse [1/min]; use of sedatives or anticonvulsants; number of hospital admissions in past 12 months; urinary incontinence in past 12 months		x				
	Medication use (type, dosage, frequency)			x		x	x
	Neuropsychological status						
	Depressive symptoms: Center for Epidemiologic Studies Depression Scale, 10 item Version [CES-D 10] [80]		x				
	Cognitive status: Montreal Cognitive Assessment [MoCa] [81]		x				
S	Fear of falling: Short Falls Efficacy Scale International [Short FES-I] [53]			x		x	x
	Motor function						
	Occurrence of dizziness or gait insecurity in past 12 months		x				
S	Balance self-efficacy: Activities-specific Balance Confidence Scale [ABC-Scale] [58]			x		x	x
S	Functional mobility: (instrumented) Timed Up-and-Go Test [34]	x		x		x	x
S	Functional capacity: Late-Life Function and Disability Instrument [LLFDI] [57]			x		x	x
S	Static balance: 8 Level Balance Scale [29]			x		x	x
S	Static balance: (instrumented) Modified Clinical Test of Sensory Interaction on Balance [54]			x		x	x
S	Static balance: (instrumented) tandem stance with eyes closed			x		x	x
S	Functional leg strength: (instrumented) 30 s chair rise [55]			x		x	x
S	Gait performance: (instrumented) 7 m walking test (usual and fast pace)			x		x	x
S	Handgrip strength: dynamometer			x		x	x
	Health status and economics						
	Subjective health: *Compared with other people in your age group, how would you rate your personal health?*		x				
P	Health-related quality of life: EQ-5D-5 L and EQ-VAS [50]			x		x	x
S	Health-related resource use: adapted version of the questionnaire for the use of medical and non-medical services in old age [FIMA] [59]			x		x	x
	Physical activity status						
	Participation in regular exercise activities > 1/week in the past 3 months; Execution of > 150 min/week moderate to vigorous physical activity	x					
P/ S	Accelerometer-collected physical activity (energy expenditure; duration, percentage, and intensity of sedentariness, activity, and walking)			x		x	x
	Psychosocial questionnaires						
S	Subjective (felt) age: visual analogue scale and years			x		x	x
S	HAPA-related questionnaires: Intention, action and coping planning, individual action control, sources of self-efficacy [60]			x	x^c^	x	x
	HAPA-related questionnaires: outcome expectations, risk perception [60]			x			
S	HAPA-related self-efficacy: motivational, maintenance, recovery [60]			x		x	x
S	Habit strength: Self-Report Behavioural Automaticity Index^e^ [SRBAI] [40]			x	x^c^	x	x
S	Motivational quality: Behavioural Regulation in Exercise Questionnaire [BRE-Q-3] [62]			x			x
S	Social support: Loneliness Scale [61]^e^			x		x	x
	Affiliative Tendency and Sensitivity to Rejection Scale [82]			x			
	Psychological Need Satisfaction in Exercise Scale [83]				x^b,c^		
	Group cohesion: Cohesion in teams–Leisure and health sport [KIT-FG] [84] (only gLiFE participants)^e^				x^a,c^		
	Adherence and group evaluation						
S	Exercise adherence: Exercise Adherence Rating Scale^d,e^ [EARS] [63]				x	x	x
	Evaluation of the intervention session: school grades scale^e^				x^a–c^		
	Satisfaction with the LiFE program^e^				x^c^	x	
	Questions on motivation of participants (only trainers)^e^				x^a–c^		

^a,b,c^*:* session number, after which the respective questionnaire is administered

^d^: part of monthly-returned fall calendar over 12 months

^e^: included in process evaluation

^f^: if > 160 / 90, the person’s general practitioner has to provide consent for participation

*BA* baseline assessment, *FU6* 6 month follow-up, *FU12* 12 month follow-up, *Int* within-intervention assessments, *IS* inhouse screening, *P* primary outcome measure (or part of it), *S* secondary outcome measure, *TS* telephone screening

#### Primary outcome measures

Fall incidence: expressed as number of falls in relation to total energy expenditure. Clinical relevance and sensitivity of this combined index has been validated recently in a cohort of 1214 community-dwelling older adults in Germany [26].

Falls will be assessed based on the fall definition provided by Lamb et al. [43], using an established procedure, i.e., a fall calendar which is returned to the respective study centre on a monthly basis for a period of 12 months. If a person has fallen, information on date, time, injuries and subsequent treatment related to the fall, location of the fall, and movement during which the person has fallen has to be provided on the sheet. In congruence with recommendations [15], a telephone-interview will be performed to rectify missing data, to ascertain details on injuries, and to confirm the current health status of the person. Injurious falls will be categorized according to a standardized system [44].

Physical activity will be assessed using “activPAL4™ micro” accelerometers (PAL Technologies Ltd., Glasgow, Scotland). It is a light, small sized (45 × 25 × 5 mm) triaxial accelerometer worn on the central front thigh over a period of 9 consecutive days (i.e., 7 days with complete data over 24 h). Body posture (sitting/lying, standing/upright) and walking activity are derived from raw data. The device has shown good to excellent reliability [45, 46] and criterion validity in identifying metabolic equivalent of task values [47] as well as body postures [48].

Cost-effectiveness: Cost-effectiveness will be assessed by the incremental cost-effectiveness ratio (ICER) represented by the ratio of the difference in costs and the difference in health effects between both interventions. Costs include in- and outpatient treatment, formal and informal care, transportation and medication as well as intervention costs due to labour costs, room hires, transportation of staff and participants, and material costs. Health effects are measured using quality-adjusted life years (QALYs) based on the EQ-5D-5 L [49, 50]. German values sets for the EQ-5D-5 L have been published recently [51]. The concept of QALYs is commonly used in health economic evaluation for measuring health effects. It combines health-related quality of life with length of life and enables comparing health effects across different diseases [52].

#### Secondary outcome measures

Secondary outcome measures are pointed out in Table 4. Fear of Falling will be assessed using the Short Falls Efficacy Scale International [53]. Motor function will be assessed in terms of instrumented (i.e., smartphone-supported) gait, functional mobility, functional strength and balance tests using the Timed Up-and-Go Test [34], 8 Level Balance Scale [29], Modified Clinical Test of Sensory Interaction on Balance [54], tandem stance with eyes closed, 30-s chair rise [55], and 7 m walking test at usual and fast pace. The smartphone will be worn in an elastic band around the waist during the tests and will provide information on a variety of movement-related parameters, e.g., trunk sway, sit-to-stand duration, jerk during sit-to-stand, and step time [56]. Handgrip strength will be measured with a JAMAR hand dynamometer. Subjective functional capacity will be assessed by the Late-Life Function and Disability Instrument (LLFDI) [57]; balance self-efficacy is assessed using the Activities-specific Balance Confidence Scale [ABC-Scale] [58]. Health-related resource use will be assessed using an adapted version of the questionnaire for the use of medical and non-medical services in old age [FIMA] [59]. Secondary parameters of PA include accelerometer-derived total energy expenditure as well as duration, percentage, and intensity of sedentariness, activity, and walking. Psychosocial evaluation of intervention effects include subjective age, HAPA-related questionnaires on intentions, action and coping planning, individual action control, sources of self-efficacy, outcome expectations, risk perception, and self-efficacy related to motivation, maintenance, and recovery [60]. Further, social support (Loneliness Scale [61]), habit strength (Self-Report Behavioural Automaticity Index; SRBAI [40]), and motivational quality (Behavioural Regulation in Exercise Questionnaire; BRE-Q-3 [62]) will be assessed. Exercise adherence will be part of the study procedure and an outcome measure in this trial. It will be assessed using the Exercise Adherence Rating Scale (EARS) [63] as part of the monthly-returned fall calendar. An additional evaluation of intervention sessions and assessment of psychosocial variables related to execution and habitualization of LiFE activities will be conducted during the intervention period.

#### Process evaluation

The MRC process evaluation framework emphasises the relations between *implementation* (what is implemented, and how?), *mechanisms of impact* (how does the intervention produce change?), *and context* (how does the context affect implementation and outcomes?) [31]. The process evaluation will complement evidence emerging from the trial. Quantitative measures used to assess these factors are marked in Table 4. Qualitative data will be gathered from focus groups which will be held within the study period. *Implementation* requires capturing whether the intervention was delivered as intended and in which quantity it was delivered. *Mechanisms of impact* will be explored using qualitative and quantitative outcome data related to the complex pathways leading to intervention-induced change. *Context* refers to external factors which may act as barriers or facilitators to intervention implementation, e.g., socioeconomic and social factors.

### Participant timeline

Screening procedure includes a telephone screening and a subsequent inhouse screening to determine eligibility. Telephone screenings will be performed to pre-screen potential participants regarding those in- and exclusion criteria that are measurable via telephone interview (see Table 4 for all variables). Those still eligible for participation will then be invited to the inhouse screening. In the inhouse screening, remaining exclusion criteria (labelled in Table 4) will be assessed to determine definitive eligibility for participation in the study. In case of medical uncertainties, the study’s medical advisor will be consulted; if the medical advisor is uncertain, the potential participant’s general practitioner will have to provide consent. Persons with a positive overall screening will then be scheduled for baseline assessment. As part of this assessment, participants will be equipped with a fall calendar for 1 year, an activPAL to assess PA for 9 days, and an activity diary to complement sensor-assessed PA measurement. After baseline assessment, participants will be randomized into either gLiFE or LiFE. The intervention is delivered as presented above. Post-assessments will be performed 6 months (follow-up 1; ± 2 weeks) and 12 months (follow-up 2; ± 2 weeks) after intervention start. All three assessments will last about 2 h each. Figure 1 gives an overview of the flow of participants.

Reasons for study drop-out or intervention drop-out will be recorded. In case of withdrawal from intervention, patients will still be eligible to participate in follow-up assessments given their consent. Reasons and date of withdrawal will be recorded in the database management system. Data recorded prior to withdrawal will be used unless the participant makes use of her/his right to have all data deleted.

### Sample size

The sample size was calculated using Pearsons’s Chi-square test, yielding *N* = 81 participants per group to be able to show noninferiority between treatments, accepting a non-inferiority margin of 20% difference to the reduction demonstrated in the original LiFE study [29]. Considering a drop-out rate comparable to the original LiFE study of 25% for all assessments [29], actually *N* = 108 participants per group are needed. To account for an additional variance due to the multi-centre design we increased the sample size by 10% and added another safety margin, coming out with an envisaged sample of a total of *N* = 300 community-dwelling participants to take part in the study: *n* = 150 at both study sites, i.e., the Network Aging Research (Heidelberg, Germany) and the Robert Bosch Hospital (Stuttgart, Germany).

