### Statistical analyses

Statistical analyses will follow the ICH Harmonized Tripartite Guideline “Statistical Principles for Clinical Trials” E9 [64]. Based on the trial of Clemson et al., we expect a decrease in fall incidence (expressed as falls per amount of PA) of 79.4% for LiFE [29]. A one-sided Pearson’s chi-square test will be used to test noninferiority with α = 0.05 in the fall incidence between LiFE and gLiFE with a noninferiority margin of − 15.9%.

All main analyses will be done according to the intention-to-treat principle, which will include all randomized participants in the analysis dataset for whom a baseline assessment was conducted, regardless of their adherence to and compliance with the assigned treatment. Participants who withdrew or dropped out are requested to participate in follow-up assessments; those who are lost to follow-up will be included in the full analysis set by imputing their missing data. Secondary analyses will provide a more detailed insight on which dimensions both treatments are effective to deepen the understanding of trial results. Understanding the underlying physiological pathways in both formats will increase knowledge on the effectiveness of the intervention components and strategies and thereby improve the design and implementation of both LiFE treatments. Additionally, sensitivity analyses will be performed to explore the effect of missing values and attrition during treatment:Per-protocol analysis of the dataset restricted to all participants with available measurements for the primary variables and no protocol violations.If the number of missing values is substantial (higher than 5% for a given variable), a sensitivity analyses will be conducted for imputing missing values.

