The LiFE program—as an exercise approach focused on the modification of individuals’ behaviour—has shown its effectiveness in a large randomised controlled trial, and it has been explicitly recommended for implementation as part of therapy practice to reduce fall risk in one of the aforementioned systematic reviews [67]. LiFE has shown its superiority relative to placebo and structured exercise [29], so assuming that LiFE *is* effective, the next step would be to look at its suitability for the recommended implementation on a large scale. Because LiFE requires seven individual one-to-one home visits, the program’s feasibility and affordability in everyday practice can be challenging. An economic evaluation of the LiFE program or a less costly alternative has never been conducted, despite the fact that the impact on both health outcomes and costs needs evaluating across competing interventions to enable well justified allocation decisions [52]. Therefore, a group-based LiFE approach should be tested for its noninferiority compared to the original, individually delivered LiFE program. Noninferiority trials aim to determine whether one treatment is not worse than a reference treatment by a predefined acceptable amount [32]. This kind of research is conducted on the premise that the “new” treatment has some other advantage compared to the reference treatment, for example less invasiveness and greater ease of administration [32]. In our study, gLiFE’s noninferiority in terms of fall incidence is evaluated with reference to the original LiFE program (LiFE): gLiFE will be recommended if it is not worse than LiFE by more than the predefined margin (∆ = 15.9%). As only a few studies of fall-related interventions have assessed costs and effects (e.g. in terms of QALYs) [70], and results were heterogeneous [73, 74], economic evaluations are needed to guide health care resource allocation.

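### The 81 per group (108 after drop-out) was sized for a proportion, but the primary outcome is a fall rate, so it does not show that noninferiority can be demonstrated on that outcome

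*Protocol article*

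**What the plan says.** The Sample size section states the method: "The sample size was calculated using Pearsons’s Chi-square test". The result is 81, given as the number of "participants per group to be able to show noninferiority between treatments, accepting a non-inferiority margin of 20% difference to the reduction demonstrated" by the earlier LiFE trial. A 25% drop-out rate raises this to 108. A further 10% for the multi-centre design and an unquantified safety margin lead to 300 in total, and the Interventions section gives 150 per arm.

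The Statistical analyses section supplies the effect: "we expect a decrease in fall incidence (expressed as falls per amount of PA) of 79.4% for LiFE". It also fixes the test: "A one-sided Pearson’s chi-square test will be used to test noninferiority", one-sided at 5% with a margin of 15.9%. The Discussion repeats the decision rule: "gLiFE will be recommended if it is not worse than LiFE by more than the predefined margin (∆ = 15.9" per cent).

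Under Primary outcome measures, fall incidence is "expressed as number of falls in relation to total energy expenditure", with falls taken from monthly calendars over 12 months. The article defines no binary primary outcome, such as faller yes/no or responder yes/no. It states no power, expected fall rate or dispersion.

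**The concern.** A Pearson chi-square test compares shares of participants. The 79.4% is not a share of participants. It is a percentage decrease in a rate, and a rate reduction does not have the variance p(1 − p). The outcome is a recurrent count divided by a continuous exposure. The precision of a comparison of such rates depends on how many falls occur, how unevenly they are spread across participants, and how much exposure each participant contributes. If the size was derived without these quantities, the statement that 81 per group is enough for noninferiority has no basis for the endpoint on which gLiFE will be recommended or not, and the power for that endpoint is unknown.

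The same mismatch sits in the analysis. The Statistical analyses section applies the chi-square test to the fall-incidence comparison itself, so sizing and test agree with each other but neither fits the outcome.

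A smaller point in the same direction: the Discussion says the original trial evaluated falls per total observation time, yet the 79.4% credited to it is expressed per amount of physical activity. The article does not explain the step between the two.

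**Working it through.** **1. Reproducing 81 and 108.**

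Inputs from the article: p = 0.794 (Statistical analyses); margin 20% of that, 0.20 × 0.794 = 0.1588, printed as 15.9%; one-sided α = 0.05; drop-out 25%. Assumed: power 80%, true difference zero.

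Two-proportion noninferiority formula, per group:

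n = (z₀.₉₅ + z₀.₈₀)² × 2p(1 − p) / margin²
= (1.645 + 0.842)² × 2 × 0.794 × 0.206 / 0.1588² = 80.2, rounded up to 81.

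With the rounded margin 0.159 the value is just above 80.0, again 81. Drop-out: 81/0.75 = 108. Both printed figures match.

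Variants on the same p do not give 81:

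| Change | n per group |
|---|---|
| power 85% | 94 |
| power 90% (margin 0.1588) | 112 |
| one-sided α 0.025, power 80% | 102 |
| absolute margin 0.20, power 80% | 51 |
| continuity correction | 93 |

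So, on the article's own inputs, the derivation is a binomial one with 0.794 × 0.206 as the variance term.

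**2. The same margin on the rate scale.**

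A 79.4% reduction leaves a rate of 1 − 0.794 = 0.206 relative to no intervention. Losing 15.9 points leaves 0.206 + 0.159 = 0.365. The margin as a rate ratio, gLiFE over LiFE, is 0.365/0.206 = 1.77, with ln(1.77) = 0.572.

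**3. Power for a rate.**

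For a negative binomial count with mean μ per participant and dispersion k, true ratio 1 and n per arm:

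SE(log rate ratio) = √[2(1/μ + k)/n]; power = Φ(0.572/SE − 1.645).

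The article gives neither μ nor k, so I assume μ = 0.5 to 1.5 falls per year and k = 1 to 2. The number analysed is 150 × 0.75 = 112.5, taken as 112. Exposure is treated as equal and known, and no clustering is included.

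Example, μ = 1.0 and k = 1: SE = √(2 × 2/112) = 0.189; 0.572/0.189 − 1.645 = 1.38; power 92%.

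| μ | k | Power, 81 per arm | Power, 112 per arm | n per arm for 80% |
|---|---|---|---|---|
| 0.5 | 1 | 68% | 80% | 114 |
| 0.5 | 2 | 57% | 69% | 152 |
| 1.0 | 1 | 82% | 92% | 76 |
| 1.0 | 2 | 68% | 80% | 114 |
| 1.5 | 1 | 88% | 95% | 63 |
| 1.5 | 2 | 72% | 84% | 101 |

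The required n runs from 63 to 152 over this modest range. On a wider one (μ 0.3 to 2.0, k 0 to 3) it runs from 19 to 240. The quantities left out of the calculation are the ones that decide the answer.

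**The case against.** The strongest reply is that nothing is miscalculated: 81 and 108 are both right for the test named, and the planned analysis uses that same test. That stands. The fault is a mismatch between endpoint and method, not a slip of arithmetic, and it follows that revising the Sample size section alone would leave a count-based size beside a chi-square analysis.

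Second, the trial plans 150 per arm, not 81. At the article's own margin, 112 analysed per arm reach about 80% or more in five of the six assumed settings. Counting 112 is also cautious: the article keeps data recorded before withdrawal and imputes for those lost to follow-up. If all 150 per arm contributed fully, an upper bound, the range would be about 80% to 99%. This stands too, and it is why the point concerns the justification rather than the number enrolled.

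Third, a condensed article may leave fall rate and dispersion to the full protocol or analysis plan. That excuses their absence. It does not make a binomial derivation valid for a rate, and the article states both the derivation and the test.

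Several stronger readings are tempting but not supported:

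- **That 300 is too few.** The table does not show this.
- **That power is far lower because 20% of the effect should be taken on the log-rate scale.** That would give a margin of 0.206^(−0.2) = 1.37. The article sets the margin as 20% of the percentage reduction, 15.9 points, and nothing in it points to a log scale.
- **That 81 can arise in no other way.** Power is not stated, so this cannot be claimed; 80% was chosen because it returns the printed figure.
- **That a failed noninferiority result could not be interpreted.** Its confidence interval could still be read against the margin.

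**Conclusion.** The point holds as a defect in the justification. The 81 and 108 come from a binomial calculation in which a relative rate reduction stands in for a proportion. They do not establish that noninferiority can be shown for falls per energy expenditure, and the article gives no power for that endpoint at N = 300.

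The size of the consequence is uncertain. With a rate-ratio margin of about 1.77, one-sided 5%, equal true rates, and assumed 0.5 to 1.5 falls per year with dispersion 1 to 2, power is about 69% to 95% with 112 analysed per arm. This is before any correlation within the gLiFE groups of 8 to 12, for which the article gives no figure, and before error in measuring exposure. Whether 300 is adequate therefore remains open and cannot be settled from the article.

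**What to change.** - Withdraw 81 and 108 as the justification of the sample size.
- State the margin as a rate ratio (about 1.77 if the percentage-reduction scale is kept), with the assumed fall rate, dispersion, one-sided α and power and the source of each.
- Report the power that the fixed N = 300 gives after drop-out, over a range of fall rates and dispersions, with an allowance for gLiFE group clustering.
- In the Statistical analyses section, replace the chi-square test by a count model, for example negative binomial with physical-activity exposure as offset, and judge noninferiority by the confidence limit of the rate ratio. Alternatively, define a binary primary endpoint that fits the chi-square test, with a proportion and margin that belong to it.

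The cost is a rewritten sample-size paragraph and a matching change to the primary analysis. Enrolment is unaffected. The downside is that the reported power may be less favourable than the present text suggests.
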